#### 2.13.2. Statistical method and analysis

Statistical analysis of the collected data will be performed using IBM SPSS Statistics 27 (IBM Corp, Armonk, USA). An intention-to-treat approach will be used in this study. All randomized subjects will be included in the analysis, regardless of whether they received treatment. In addition, interim analyses will not be performed.

Descriptive statistics will be used to summarize participants baseline characteristics by group using mean (standard deviation), median (interquartile range), or number (percentage) as appropriate. All measurement data will first be assessed using normality tests. One-way analysis of variance or Welch analysis of variance will be used for comparison among the 3 groups for continuous variables. Categorical variables will be compared using the Pearson chi-squared test (or Fisher exact test).

Analyses of the primary and secondary continuous outcome variables among the 3 study groups (EA, EAWN, and waitlist control) overtime (baseline, weeks 5 and 10) will be performed using linear mixed models for repeated measures analysis, with treatment, time point, and interaction between treatment and time point included as fixed effects, within-person correlation modeled as a random effect, and age and tinnitus duration adjusted as covariates in the model. Missing data will be processed using the mixed effects model, assuming missing at random. Significant results (significant interaction, time × study groups) will be subject to post hoc tests to determine which group scores differently. Mean differences at weeks 5 and 10 will be estimated by the treatment × time interaction term, with associated 95% confidence intervals and *P* values.

Comparisons between the EA and EAWN groups for the adverse event rate among the 3 groups will be evaluated using the Pearson chi-squared test (or Fisher exact test).

The results will be considered statistically significant at a probability level of *P* < .05 with a 2-sided test throughout the analysis. In post hoc tests, we will employ the Bonferroni correction method and appropriately adjust the overall level of significance for multiple primary and secondary outcomes at different time points.

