#### 2.9.1. Primary outcome

Tinnitus loudness is a main symptom of tinnitus. The primary endpoint of our study will be the change in NRS score for tinnitus loudness from baseline to treatment completion (week 5). Changes in the mean NRS score for tinnitus from baseline to week 10 (5 weeks after treatment completion) will also be assessed. The NRS for the loudness of tinnitus is a widely used measurement for tinnitus.^[2]^ Subjects will rate the loudness of tinnitus using an 11-point NRS (0 − 10) with 0 indicating “no tinnitus”, and 10 indicating “maximum intolerable tinnitus”. The higher the score, the greater the tinnitus loudness and its effect.

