### 2.13. Statistical analysis

#### 2.13.1. Sample size calculation

The sample size calculation will be based on the primary outcome measure of the NRS score of the loudness of tinnitus (0 − 10 points) and performed using OpenEpi.^[35]^ An estimation of the between-group difference and standard deviation is necessary because of the lack of similar comparable studies. In this study, we assume that similar differences in the NRS score of tinnitus loudness will be detected between the EA and waitlist control groups or the EAWN and waitlist control groups. We presume that a clinically significant difference of mean 2-point reduction and standard deviation of 2.49 in the NRS score of tinnitus loudness is detected based on previous studies^[36,37]^ and expert opinion. Using a 2-sided test, an alpha value of 0.05, and a power of 80%, it is estimated that 25 subjects will be required per study group. Considering a 20% attrition rate, the sample size for each group will be 30 subjects, which implies a total sample size of 90 subjects for the entire trial.

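### The planned week-5 interaction is a plain change-score comparison: valid, but less precise than one that estimates the baseline slope, and age and duration as listed hardly adjust it

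*Protocol article*

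**What the plan says.** Section 2.9.1 of the protocol article sets the primary endpoint as the "change in NRS score for tinnitus loudness from baseline to treatment completion (week 5").

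Section 2.13.2 then specifies the model in some detail:

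- **Responses:** the three-group analyses "overtime (baseline, weeks 5 and 10) will be performed using linear mixed models for repeated measures analysis", so baseline is one of the modelled outcomes.
- **Fixed effects:** the model is fitted "with treatment, time point, and interaction between treatment and time point included as fixed effects". The arms are therefore free to differ at baseline.
- **Correlation:** "within-person correlation modeled as a random effect", most naturally a random intercept.
- **Covariates:** "age and tinnitus duration adjusted as covariates in the model". No baseline score is listed as a covariate, and the only interaction named is treatment by time.
- **Estimator:** "Mean differences at weeks 5 and 10 will be estimated by the treatment × time interaction term".

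The same model serves the primary outcome (NRS) and the secondary outcome (THI).

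**The concern.** Responses, fixed effects and estimator are all named, so one can work out what the primary result will be. Two features deserve attention.

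First, the model does not use the fact that randomisation gives the arms equal expected baseline means. Baseline is subtracted in full, whatever its actual relation to the week-5 score. With 30 patients per arm, chance baseline differences will occur, and full subtraction can over-correct them when the true regression slope is below 1.

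Second, a covariate that is constant within a person and enters only as a main effect shifts all of that person's visits equally, so it drops out of a change. The report would describe a result adjusted for age and tinnitus duration when that adjustment barely touches the primary contrast.

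At stake are precision and an accurate description of the analysis, not the validity of the test.

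**Working it through.** **Inputs.** From section 2.13.1: "a clinically significant difference of mean 2-point reduction and standard deviation of 2.49 in the NRS score of tinnitus loudness"; "Using a 2-sided test, an alpha value of 0.05, and a power of 80" percent; 25 per group, raised to 30 for 20% attrition. From section 2.13.2: the model above. From section 2.2.1: entry requires NRS of at least 3 on the 0 to 10 scale. Not in the documents, hence assumed: the baseline to week-5 correlation r, and k, the baseline SD divided by the week-5 SD.

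**1. The plan's own figure.** n = 2 × (1.96 + 0.84)² × 2.49² / 2² = 24.3, rounded up to 25 per group. The stated number is reproduced, with 81% power by the normal approximation.

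**2. What the interaction estimates.** With complete data and a saturated group by time mean, the fitted mean for group g at visit t is the observed mean minus γ times the group's mean covariate value. That second term is the same at every visit. The week-5 interaction is therefore

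(active week 5 − active baseline) − (control week 5 − control baseline),

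the raw difference in mean change. γ has cancelled.

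**3. Check by simulation** (30 per arm, three visits, random intercept, REML, score SD 2.49, equal SDs, 100 trials per setting). With complete data the interaction matched the raw change difference to about 1e-13, with or without age and duration. The mean SE was the same either way. With about 20% dropout by week 10, the covariates moved the estimate by at most about 0.11 points and left the mean SE unchanged to three decimals.

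| r | Planned SE, complete | Common-baseline SE, complete | Planned SE, dropout | Common-baseline SE, dropout |
|---|---|---|---|---|
| 0.3 | 0.754 | 0.612 | 0.802 | 0.664 |
| 0.5 | 0.642 | 0.558 | 0.681 | 0.602 |
| 0.7 | 0.497 | 0.458 | 0.534 | 0.498 |

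**4. Size of the gain.** With week-5 SD s and baseline SD ks:

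- change-score variance: s²(1 + k² − 2rk)
- baseline-adjusted variance: s²(1 − r²)
- ratio, adjusted to planned: (1 − r²)/(1 + k² − 2rk), which is (1 + r)/2 when k = 1

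| r | k = 1 | k = 0.8 | k = 0.7 |
|---|---|---|---|
| 0.4 | 0.70 | 0.84 | 0.90 |
| 0.5 | 0.75 | 0.89 | 0.95 |
| 0.6 | 0.80 | 0.94 | 0.985 |
| 0.7 | 0.85 | 0.98 | 1.00 |

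The regression slope is r/k. At r = k = 0.7 it equals 1, and the change score is then already the best linear use of baseline. A k below 1 is plausible because the entry threshold cuts off low scores at baseline but not at week 5.

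**5. Power, for illustration.** Assume 24 per arm (30 less 20%), a difference of 2, 2.49 as the SD of change, k = 1 and the noncentral t. The adjusted SD is 2.49 × √((1 + r)/2).

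| Two-sided alpha | Planned | r = 0.4 | r = 0.5 | r = 0.6 | r = 0.7 |
|---|---|---|---|---|---|
| 0.05 | 78% | 90% | 88% | 86% | 84% |
| 0.025 (assumed Bonferroni, two comparisons) | 68% | 84% | 81% | 78% | 76% |

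With k = 0.8 and alpha 0.05, the same calculation with SD 2.49 × √ratio gives 84%, 82%, 80% and 78% against the planned 78%.

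If 2.49 is instead the SD of the score (k = 1, alpha 0.05), the SDs are 2.49 × √(2(1 − r)) planned and 2.49 × √(1 − r²) adjusted. At r = 0.4 these are 2.73 and 2.28, giving power of 70% and 84%. At r = 0.7 they are 1.93 and 1.78, giving 94% and 97%.

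**The case against.** The endpoint is defined as a change, the interaction estimates that change, and this is a standard model. Nothing is contradicted. All of this stands, so the point concerns efficiency and labelling only.

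A reader might go further and infer that baseline NRS is discarded, that chance imbalance goes uncorrected, or that the result is biased. The documents do not support this. A change score removes the raw imbalance in full. Its fault is that the slope is fixed at 1, so it may remove too much, and over repeated randomisations the estimate is unbiased.

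A reader might also infer from the 68% that the trial is badly underpowered because of this model. That figure needs alpha 0.025, whereas section 2.13.1 plans at 0.05 and section 2.13.2 gives no Bonferroni divisor. At 0.05 the planned contrast has 78% under the same assumptions. Most of the distance from 80% to 68% is multiplicity, a separate matter.

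The gain could also be small. Equal SDs are the favourable case; at k = 0.7 the saving is 10% of variance at most and can be nil.

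Lastly, main effects only is the natural reading of the listed terms but is not stated in so many words, and a fuller analysis plan could contain covariate by time terms. Exact cancellation also needs complete data, so with dropout the covariates are not strictly without effect. Nor do the documents show that duration drives spontaneous change. These points limit the covariate criticism but do not remove it: as the text stands, the adjustment does almost nothing to the primary contrast.

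**Conclusion.** The point holds as an inexpensive improvement, not as an error. It rests on reading the random effect as a random intercept and the covariates as main effects. On that reading the identity with the raw change difference is exact for complete data and approximate with missing visits.

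The precision forgone is 15% to 30% of variance for r = 0.7 to 0.4 with equal SDs, and 2% to 16% if the baseline SD is 0.8 of the week-5 SD. Neither r nor the SD ratio is in the protocol, and section 2.13.1 does not make clear whether 2.49 is the SD of the score or of the change. The algebra is therefore certain and the size is not.

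In large samples an estimated slope is never less precise than a slope fixed at 1, so the change carries little risk.

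**What to change.** In section 2.13.2, choose one of two models, for both NRS and THI:

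1. Keep baseline, week 5 and week 10 as responses, but constrain the three arms to a common baseline mean. In practice, drop the treatment main effect and code four indicators (two active arms by two post-baseline visits). Every randomised subject with a baseline score stays in the analysis.
2. Use weeks 5 and 10 only as responses, with baseline score and baseline score by time as covariates.

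If age and tinnitus duration are meant to adjust the treatment effect on change, add their interactions with time. Under option 1 this costs four parameters (two covariates by two post-baseline visits). Under option 2 their main effects no longer cancel, and the time interaction (two parameters) lets their effect differ between visits. If no such adjustment is intended, the result should not be described as adjusted for them.

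The cost is a few words of text and a different model statement in the same software. Baseline NRS, baseline THI and age are already collected, and tinnitus duration is already needed for eligibility and for the planned model. Trial conduct does not change.

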## 2. Methods

### 2.1. Study design and setting

This study is a prospective, multicenter, assessor-blind, triple-arm, parallel-group, randomized controlled trial with a 1:1:1 ratio of group allocation to EA, EAWN, or waitlist control (control group, who can receive acupuncture treatment after a 10-week waiting period). Ninety eligible participants will be recruited for this study. The entire study period will last for 10 weeks, including a 5-week intervention period and a 5-week follow-up period. Outcome assessments will be performed at baseline and at weeks 5 and 10 through telephone or face-to-face evaluations. The study will be conducted at 3 Chinese medicine clinics under the management of Pok Oi Hospital, namely, Pok Oi Hospital − The Chinese University of Hong Kong Chinese Medicine Clinic cum Training and Research Centre (Shatin District), Pok Oi Hospital − The Chinese University of Hong Kong Chinese Medicine Clinic cum Training and Research Centre (Yuen Long District), and Pok Oi Hospital − Chinese Medicine Polyclinic (Tin Shui Wai). The study protocol is written following the Standard Protocol Items: Recommendations for Interventional Trials 2013 Statement and the Standard Protocol Items for Clinical Trials with TCM 2018 checklists.^[15,16]^

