### 2.3. Recruitment procedure and study flow

Subjects will be recruited from all Chinese medicine centers, polyclinics, and mobile clinics under the management of Pok Oi Hospital. These sites cover all districts in Hong Kong. Subjects interested in participating in the study will be referred to or self-approached by the 3 dedicated Chinese medicine centers to undergo eligibility assessment. They will be prescreened through telephone interviews. Potential participants will undergo a face-to-face interview to confirm their eligibility for the study. During the interview, the investigators will explain the overall objectives and nature of the study, and undergo the eligibility assessment and informed consent process. A 4-week washout period will be required for those receiving acupuncture therapies before enrollment. If the subject consents, sociodemographic and clinical data, including sex, age, and medical history will be collected. Additionally, baseline assessments of primary and secondary outcome measures will be conducted. They will then be randomly assigned to 1 of the 3 groups by an independent staff member who is not involved in the study. A schedule for treatment and follow-up procedure will be assigned. After enrollment, the study site will strive to keep track of the participants throughout the study to maintain participation and complete follow-up assessments. The study flow is shown in Figure 1 and Figure 2 demonstrates the schedule of enrollment, interventions, and assessments.

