### 2.4. Randomization and blinding

The treatment allocation of EA, EAWN, or waitlist control for each eligible subject in the study will be determined through a randomization process. Participants will be told that they will be randomized to 1 of 3 groups: EA for 5 weeks followed by observation for 5 weeks; EAWN for 5 weeks followed by observation for 5 weeks; or observation for 10 weeks followed by EA or EAWN for 5 weeks. Treatment or assessment will be scheduled to avoid contact between the participants. The random allocation to the 3 arms of the study will be generated using Random Allocation Software,^[17]^ following a balanced 1:1:1 ratio. A standard block size of 6 will be used, which will not be revealed to the site investigators. This will be performed by an independent administrator who is not involved in the study, and the information on the random allocation list will remain strictly confidential. The randomization result will be kept in sequentially numbered, opaque, sealed envelopes to ensure allocation concealment. In this study, practitioners and patients will not be blinded; however, the outcome assessors will be blinded to the intervention assignment.

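### A three-clinic trial whose stated model omits clinic: a modest, avoidable loss of precision wherever clinics differ in change

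*Protocol article*

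**What the plan says.** Section 2.1 calls the trial multicentre and names the sites: "The study will be conducted at 3 Chinese medicine clinics under the management of Pok Oi Hospital". Section 2.3 describes a shared recruitment pool: "Subjects will be recruited from all Chinese medicine centers, polyclinics, and mobile clinics under the management of Pok Oi Hospital". Interested people then reach one of the three study clinics by referral or on their own initiative.

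On allocation, section 2.4 says "The random allocation to the 3 arms of the study will be generated using Random Allocation Software", "following a balanced 1:1:1 ratio", and "A standard block size of 6 will be used, which will not be revealed to the site investigators". Results are held in numbered sealed envelopes. No stratification factor is named and no per-clinic list is mentioned.

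On analysis, section 2.13.2 spells out the model: fixed effects "with treatment, time point, and interaction between treatment and time point included as fixed effects", a random effect for within-person correlation, and age and tinnitus duration as covariates. The treatment effect at weeks 5 and 10 is read from the treatment × time term. Clinic does not appear.

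**The concern.** The article names its covariates, so it has fixed a model that leaves clinic out; this is not a detail left open. Adding clinic after the data have been seen would be a post hoc choice.

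Change could plausibly differ by clinic. Section 2.6.1 describes manual treatment: needles are twirled to elicit a sensation, current is adjusted to each patient's tolerance, and moxa is placed by hand. The outcome is a self-rating by unblinded patients. Any clinic difference in change stays in the residual of the primary contrast. If blocks are not formed within clinic, chance can also put more of one arm in a clinic that responds better or worse.

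Precision is what is at stake, in a trial planned at 80% power with 25 evaluable patients per arm.

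**Working it through.** **Inputs from the article.** Three clinics (2.1); 1:1:1 in blocks of 6 (2.4); difference 2 points, SD 2.49, two-sided alpha 0.05, power 80%, 25 per group, 20% attrition, 30 per group (2.13.1).

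**Assumptions, not in the article.** SD 2.49 is read as the SD of change, including any clinic component. The share of that variance due to clinic, ρ, is taken as 0 to 0.15. Clinics are of equal size, and their patients draw in mixed order from one list.

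**Step 1: the plan's own figure.** n = 2 × (1.96 + 0.84)² × 2.49² / 2² ≈ 24.3, so 25 per group, as stated. Losing 20% of 30 leaves 24.

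**Step 2: which clinic differences matter.** A random-intercept model was fitted to one simulated complete data set of 90 patients, with and without a constant shift of 3 points from each clinic to the next.

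| | no shift | 3-point shift |
|---|---|---|
| treatment × time estimate | −2.583 | −2.583 |
| its standard error | 0.624 | 0.624 |
| residual variance | 2.92 | 2.92 |
| person variance | 2.10 | 7.30 |

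The person effect absorbs stable level differences. Adding a clinic main effect also left the estimate and standard error unchanged. Only clinic differences in change reach the contrast, so clinic must enter with time.

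**Step 3: chance imbalance.** With 30 patients per clinic and one unstratified list (20,000 lists), the largest and smallest arms in some clinic differ by 6 or more in about 54–55% of lists. The EA and waitlist counts differ by 5 or more in some clinic in 44%. In a separate simulation of 75 completers, the largest EA–waitlist gap at any clinic had median 4 and 95th percentile 8 (3 and 7 with a 60/30/10 split). As an illustration, suppose EA has 4 more patients than waitlist at one clinic and 4 fewer at another, and mean change differs by 1 point between those clinics. The contrast then moves by 4/25 × 1 = 0.16 points in that trial.

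**Step 4: what the assumed shares mean.** For three equal, evenly spaced clinics with effects −a, 0, a on change, 2a²/3 = ρ × 2.49², so a = 2.49 × √(1.5ρ). The two extreme clinics then differ by 2a: about 1.4 points at ρ = 0.05, 1.9 at 0.10 and 2.4 at 0.15. The top of the range is therefore generous beside a treatment effect of 2 points.

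**Step 5: power by formula.** With clinic in the model the residual SD is 2.49 × √(1−ρ). Noncentral-t power at 25 per arm, with arms balanced over clinics, is 80.0% without clinic. With clinic it is 80.0% (ρ = 0), 82.0% (0.05), 83.9% (0.10) and 85.9% (0.15). The required n falls from 25 to 24, 22 and 21.

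**Step 6: power by simulation, model change only.** 6,000 trials per setting on change scores, unstratified list, 20% loss. With complete data, clinic as a factor on change corresponds to clinic × time in the mixed model.

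| ρ (assumed) | without clinic | with clinic | difference |
|---|---|---|---|
| 0 | 78.3% | 77.0% | −1.3 |
| 0.05 | 78.3% | 79.4% | +1.1 |
| 0.10 | 78.1% | 81.7% | +3.6 |
| 0.15 | 76.7% | 81.7% | +5.0 |

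The Monte Carlo standard error is about 0.5 points per entry. A second run gave gains of 0.7, 2.8 and 4.3 points, and a small loss at ρ = 0.

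**Step 7: validity.** For ρ from 0 to 0.10, type I error without clinic was 4.6–5.5%, and the mean estimate was about −2.0 against a true −2. With equal clinics and ρ = 0.10, the SD of the estimate fell from 0.71 to 0.69 when clinic was added.

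**The case against.** The article is condensed. It is silent on strata and does not rule them out, and it does not say how envelopes were divided among clinics. If whole blocks went to each clinic, arms would be nearly balanced there and the percentages in Step 3 would not apply. This stands, and it is why the allocation half is put as something to state. The model half does not depend on it: if blocks are formed within clinic, the analysis should reflect that design factor, and the stated model does not.

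A lean model is defensible with about 25 evaluable patients per arm, common training and a standardised procedure, and nothing in the article shows that clinics differ in change. This also stands. At a 5% share the gain is close to simulation noise, and at zero there is a small loss. It limits the weight of the point without removing it.

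Three stronger readings are tempting, and the documents do not support them:

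- **Each clinic has its own practitioners and catchment.** Section 2.5 does not tie practitioners to clinics. Section 2.3 points away from separate catchments, since one territory-wide pool feeds all three.
- **All clinic differences go into error.** Stable level differences cancel (Step 2).
- **Omitting clinic biases or invalidates the test.** Allocation is randomised, and the simulations show neither bias nor inflated type I error. Chance imbalance can shift a single realised estimate, but not systematically.

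**Conclusion.** The point holds as a minor one. The trial has three clinics, the stated model adjusts for age and tinnitus duration but not clinic, and the described randomisation names no clinic stratum. Clinic differences in change would add noise to the active-versus-waitlist contrasts. Changing the model alone is worth about 1 to 5 points of power if clinic explains 5–15% of the variance of change, and costs about 1 point or less if it explains nothing. That range rests on the assumed share, on equal clinics drawing in mixed order from one list, and on reading 2.49 as the SD of change. The planned analysis remains valid without the change.

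**What to change.** In section 2.13.2, pre-specify clinic and clinic × time as fixed effects; a clinic main effect alone would not help the treatment × time contrast. In section 2.4, state whether blocks are generated within clinic. If they are not and recruitment has not begun, also stratify the allocation list by clinic, with a separate blocked list and envelope series for each. If recruitment has begun, make the model change only, before the data are unblinded.

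The cost is a line in each section and a few degrees of freedom. Clinic is already known for every patient.

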#### 2.2.1. Inclusion criteria

Participants diagnosed with subjective tinnitus^[1]^ and able to communicate normally in Chinese will be recruited in the study if they satisfied all of the following criteria: Males and females aged 50 to 70 years; Unilateral or bilateral tinnitus for 0.5 to 24 months; Loudness of tinnitus rated ≥ 3 points on a 0 to 10 numeric rating scale (NRS) at the time of enrollment; Agree to sign the informed consent form voluntarily.

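### A random person effect imposes equal variances and correlations on all three visits, so the week-5 and week-10 standard errors may be wrong, in a direction the protocol cannot settle

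*Protocol article*

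**What the plan says.** Section 2.13.2 of the protocol article treats baseline as one of three outcome visits. The scores "overtime (baseline, weeks 5 and 10) will be performed using linear mixed models for repeated measures analysis". Fixed effects are treatment, time point and their interaction, with age and tinnitus duration as covariates. The dependence between a patient's visits is handled in one phrase: "within-person correlation modeled as a random effect". No other covariance term is named.

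The effect estimates come from this model: "Mean differences at weeks 5 and 10 will be estimated by the treatment × time interaction term". The primary endpoint (section 2.9.1) is the change in loudness NRS from baseline to week 5; the change to week 10 is also assessed. Post hoc comparisons follow a significant interaction and are Bonferroni corrected.

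**The concern.** One random effect per person, with independent residuals, has two covariance parameters. It fixes a common variance at all visits and a common correlation for baseline with week 5, baseline with week 10, and week 5 with week 10. The three visits differ in kind: one before treatment, one at its end, and one after five weeks without it. Nothing in the protocol shows that they are exchangeable.

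If they are not, the estimated mean differences with complete data are unaffected, but their standard errors are wrong. The model pools the three pairwise change variances into one error term, which then serves a contrast whose true variance may be larger or smaller. The confidence interval and P value of the primary endpoint, and those at week 10, depend on it.

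**Working it through.** **The plan's own figure.** Section 2.13.1 assumes a "mean 2-point reduction and standard deviation of 2.49 in the NRS score of tinnitus loudness", two-sided alpha 0.05 and 80% power, and states that "it is estimated that 25 subjects will be required per study group". Check: n = 2 × [2.49 × (1.960 + 0.842) / 2]² = 24.33, rounded up to 25. It reproduces. It uses no visit correlation, so it neither supports nor refutes the covariance model.

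**Inputs.** The visits (0, 5 and 10 weeks) and the model are from sections 2.9 and 2.13.2. The protocol gives no visit-specific SDs or correlations, so every pattern below is an assumption.

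**Formula.** For three visits, the sum of squares about a person's own mean is one third of the sum of the three squared pairwise differences, on 2 degrees of freedom. The residual variance therefore estimates half the mean of the three pairwise change variances. The model takes twice that as the variance of any change:

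- SE ratio (model / true) at week 5 = √{mean[Var(Y5−Y0), Var(Y10−Y0), Var(Y10−Y5)] / Var(Y5−Y0)}
- actual two-sided error ≈ 2 × [1 − Φ(1.96 × ratio)]

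With equal SDs each change variance is proportional to 1 − ρ, and the SD cancels.

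**Worked cases**, correlations in the order 0–5, 0–10, 5–10:

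- 0.5/0.5/0.8: the values 1 − ρ are 0.5, 0.5, 0.2, with mean 0.400. Ratio = √(0.400/0.5) = 0.894; error 8.0%.
- Decay with ρ = 0.7 per 5 weeks (0.7/0.49/0.7): 0.30, 0.51, 0.30, with mean 0.370. Week 5: √(0.370/0.30) = 1.111, error 3.0%. Week 10: √(0.370/0.51) = 0.852, error 9.5%.

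| Assumed pattern (equal SDs) | Week-5 SE ratio | Week-5 error | Week-10 error |
|---|---|---|---|
| 0.5/0.5/0.5 | 1.000 | 5.0% | 5.0% |
| 0.5/0.5/0.7 | 0.931 | 6.8% | 6.8% |
| 0.5/0.5/0.8 | 0.894 | 8.0% | 8.0% |
| 0.5/0.5/0.9 | 0.856 | 9.3% | 9.3% |
| 0.5/0.3/0.7 | 1.000 | 5.0% | 9.8% |
| decay, ρ = 0.5 | 1.080 | 3.4% | 8.4% |
| decay, ρ = 0.7 | 1.111 | 3.0% | 9.5% |

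With equal SDs, the week-5 SE is too small only if the 0–5 correlation is below the average of the other two.

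**Simulation check.** With 40,000 null trials per pattern, 30 per arm, complete data and no covariates, the week-5 error was 5.1% (0.5/0.5/0.5), 6.6% (0.5/0.5/0.7), 8.0% (0.5/0.5/0.8), 3.3% (decay 0.5) and 2.7% (decay 0.7). In a separate run of 8,000 null trials with 25 per arm under 0.5/0.5/0.8, an unstructured covariance gave 5.1% and the random intercept 8.2%.

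**Power in the conservative case.** Assume that 2.49 is the SD of the week-5 change, with 25 completers per arm. Then 2 / (2.49 × √(2/25)) = 2.84, and correct power is Φ(2.84 − 1.96) = 81%. An SE too large by the factor 1.080 gives Φ(2.84 − 2.117) = 76%; by 1.111, Φ(2.84 − 2.177) = 75%.

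**The case against.** **The model is partly inferred.** The text does not say random intercept and gives no residual structure. A fuller protocol or analysis plan may do so, and a journal article may fairly leave such detail there. This stands as a limit on the point: it holds for the natural reading. But the article does state how the correlation is modelled, so this is a comment on a stated choice rather than on an omission.

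**The direction is not known.** A reader might infer that the primary test is likely to be anti-conservative, because the two scores after baseline should resemble each other more than either resembles baseline. The documents do not support that. They give no correlations. The visits are equally spaced, and ordinary decay over time gives the opposite at week 5. Type I error is also judged under no treatment effect, where a treatment-induced break after baseline is not an obvious pattern. This objection stands in full.

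**The entry rule does not add to the risk.** A reader might also infer inflation from the requirement "Loudness of tinnitus rated ≥ 3 points on a 0 to 10 numeric rating scale (NRS) at the time of enrollment", since it may shrink the baseline variance. It points the other way. With correlations 0.5/0.45/0.8, lowering the baseline SD from 2.49 to 1.8 moves the week-5 error from 7.4% to 6.9%. With all correlations at 0.5, the same change gives 4.1% at both weeks.

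**The figures describe one unadjusted contrast.** The planned procedure is an interaction test followed by Bonferroni-corrected comparisons. The simulated interaction test is less affected: 5.3 to 6.4% across the unequal-correlation patterns with equal SDs. Bonferroni does not repair a wrong SE, however. At 0.05/3 = 1.67%, the simulated week-5 error was 3.3% under 0.5/0.5/0.8 and 0.7% under decay with ρ = 0.7.

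**Conclusion.** The point holds in a limited form. If the phrase means a random intercept with independent residuals, the SEs of the week-5 and week-10 contrasts are right only when each contrast's own change variance equals the average of the three. Across the equal-SD patterns tabulated, the nominal 5% week-5 test ranges from about 3% to 9%. In the decay patterns, where week 5 is conservative, week 10 is anti-conservative at about 8 to 9.5%. Exchangeable visits give no error.

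These sizes rest on assumed correlations, complete data and no covariates. They do not show that the primary result would be falsely positive. They show that its SE depends on an assumption that the protocol does not support and need not make. A random-effect model is a legitimate choice for three visits; this is a cheap improvement, not a flaw that invalidates the analysis.

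**What to change.** In section 2.13.2, replace the phrase on the random effect with an unstructured within-person covariance over baseline, week 5 and week 10, fitted by REML with Satterthwaite or Kenward-Roger degrees of freedom. State that the random-intercept model is the fallback, used only if the unstructured model does not converge. Fix this before outcome data are seen.

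The unstructured form has six parameters (three variances and three covariances) instead of two, which 90 patients can support. The cost is one phrase, a few error degrees of freedom and intervals that may be slightly wider. If an unshown analysis plan already specifies this structure, the article's wording need only be aligned with it.
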